### Eligibility criteria for participants

Inclusion criteria are (1) patients aged 19 years old or older, (2) ASA physical status classification I to III, (3) elective neurovascular surgery (aneurysm clipping, microvascular decompression, superficial temporal artery to middle cerebral artery bypass, arteriovenous malformation removal, etc.) and receiving general anesthesia.

Exclusion criteria are (1) severe respiratory disease or cardiovascular disease, (2) severe hepatic (Childs-Pugh Score Class C) disease, (3) severe audio-visual impairments that impede communication, (4) hypersensitivity reactions, allergies, or contraindications to the study drugs, (5) evidence of preoperative delirium in Confusion Assessment Method (CAM), and (6) dependency on psychiatric drugs or alcohol.

Dropout criteria are (1) patient withdrawal and (2) surgery cancelation. In participants who withdraw their consent, the reason for their withdrawal will be collected and reported. They will also be asked to specify which aspects of the trial they are withdrawing their consent and participation from. They will be included in the final report of the trial to ensure complete transparency. A participant who withdraws consent for follow-up assessment will be asked about the use of outcome data and only permitted data will be used for the final analysis. All data will be analyzed according to the modified intention to treat (ITT) principle after excluding patients with drop-out criteria.

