#### Secondary outcomes

Secondary outcomes are (1) severity of delirium, (2) number of positive delirium assessment, (3) emergence agitation which is defined as RASS + 1 or more within 30 min after the endotracheal extubation, (4) delayed extubation (> 1 h after surgery), (5) perioperative adverse events including intraoperative awareness with recall or undesirable patient movement, bradycardia with the use of chronotropic agent, laryngeal spasm, bronchospasm, allergic reaction, arrhythmia, cardiac events (myocardial infarction, vasospasm, or cardiac arrest), or massive bleeding, (6) area under the mean blood pressure threshold (AUT), (7) quality of recovery using Qor-15 questionnaire (Stark et al. 2013), (8) postoperative nausea and vomiting (PONV), (9) incidence and severity of non-delirium complications (non-neurologic or neurologic) within 30 days after surgery, which are graded using Clavien-Dindo classification (Dindo et al. 2004; Landriel Ibañez et al. 2011), (10) length of hospital, defined as the number of days from index neurovascular surgery until initial hospital discharge and ICU stay, defined as the number of hours in the neurosurgical ICU following index neurovascular surgery until the initial ICU discharge, (11) changes in cognition. (12) The occurrence of fall-down and associated injury and functionality at 3 months after surgery.

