### Safety monitoring

As the administration and dosage of study medications in both anesthesia regimens are within the current clinical practice, we believe that SAEs should be rare. The adverse effects of propofol and remimazolam will be closely monitored during operation by attending anesthesiologists. In case of fetal adverse events, they could stop the infusion of study medications, request the unmaking of group allocation, and inform the principal investigator of any reason for stopping the infusion of study drugs. In addition, a designated investigator will review the occurrence of adverse events possibly caused by study drugs from the start to the end of infusion using chart review. The DMC will perform a review to ensure patient safety. Throughout the study, any adverse events should be reported within 24 h to the DMC.

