### Statistical analysis

All reported study results except adverse events and non-delirium complications are analyzed, following the modified intention-to-treat-principle (ITT). Data will be descriptively presented using summary statistics such as median and quartiles, means and SD, or frequency and percent as appropriate. The standardized mean difference (SMD) will be used for the comparison of baseline data between the randomized groups. Acceptable covariate balance is defined as a standardized mean difference < 0.2 for the entire list of covariates. Repeated measurements, such as NRS score for pain and sleep quality, daily cumulative opioid requirement, and cognitive function will be compared using generalized estimating equation (GEE) analysis among groups.

For the analysis of primary outcome, we will employ a modified ITT principle, which means all randomized participants, regardless of protocol adherence will be included in the primary analysis, except for the case with surgery cancelation and withdrawal of consent after randomization. The incidence among groups will be compared by calculating the 95% CI of the incidence difference: incidence (remimazolam group)-incidence (propofol group), and noninferiority will be achieved if the upper limit of 95% CI is < 10%. The incidence of POD will be compared using a one-sided two-sample *z*-test with an alpha level of 0.025. We will use a multivariable logistic regression model, which will adjust the treatment effect for covariates found to be imbalanced between the two groups.

For the secondary outcome, except for the analysis of intraoperative adverse events and non-delirium complications in which the PP approach will be used, a modified ITT approach will be used. Group comparison will be performed using a two-sample *t* test or Mann–Whitney *U* test as appropriate for continuous variables, and a chi-square test or Fisher’s exact test for categorical variables. We will adjust the effect of imbalanced covariates using a multivariable logistic regression model for count variables and linear regression or quantile regression for continuous variables.

Subgroup analyses will be conducted to assess the consistency of differences in the primary outcome used to differentiate the effect of treatment among different populations (age, sex, surgery type, preoperative cognitive impairment, ASA physical status, duration of anesthesia, alcohol abuse, or preoperative benzodiazepine use within 24 h).

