## Abbreviations

3D-CAM: 3-Minute diagnostic interview for Confusion Assessment Method
ASA: American Society of Anesthesiologist
BIS: Bispectral index
CAM-ICU: Confusion Assessment Method for the Intensive Care Unit
CI: Confidence interval
CRF: Case Report Form
DMC: Data Monitoring Committee
DRS: Delirium rating scale
EEG: Electroencephalogram
ICU: Intensive care unit
IRB: Institutional Review Board
ITT: Intention to treat
MoCA: Montreal Cognitive Assessment
NRS: Numeric rating scale
POD: Postoperative delirium
PONV: Postoperative nausea and vomiting
PP: Per protocol
RASS: Richmond Agitation-Sedation Scale
SAEs: Serious adverse events
SD: Standard deviation
TCI: Target controlled infusion

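### Intraoperative adverse events and non-delirium complications are assigned to a per-protocol set, which contradicts the all-data modified ITT rule and can drop patients because of the event being counted

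*Protocol article*

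**What the plan says.** The Statistical analysis section separates safety from the other results twice. Its opening sentence reads "All reported study results except adverse events and non-delirium complications are analyzed, following the modified intention-to-treat-principle (ITT"). Its paragraph on secondary outcomes then applies modified ITT "except for the analysis of intraoperative adverse events and non-delirium complications in which the PP approach will be used". The list of abbreviations expands the term ("PP: Per protocol"), but the article gives no rule for who belongs to the set.

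Two other statements bear on this:

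- Eligibility criteria for participants: "All data will be analyzed according to the modified intention to treat (ITT) principle after excluding patients with drop-out criteria". The drop-out criteria there are patient withdrawal and surgery cancelation. No exception is made for safety.
- Statistical analysis, on the primary outcome: modified ITT means that "all randomized participants, regardless of protocol adherence will be included in the primary analysis", apart from canceled surgery and withdrawn consent.

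The outcomes concerned are listed under Secondary outcomes. They are "perioperative adverse events including intraoperative awareness with recall or undesirable patient movement, bradycardia with the use of chronotropic agent" and further events such as allergic reaction, arrhythmia, cardiac events and massive bleeding, together with graded non-delirium complications up to 30 days. Under Safety monitoring, attending anesthesiologists facing certain adverse events are told that "they could stop the infusion of study medications".

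**The concern.** For an efficacy outcome, a per-protocol set removes patients whose treatment departed from plan. For a harm, the departure can be a consequence of the outcome: the event occurs, the study drug is stopped, and the patient may no longer count as treated per protocol. The event then leaves the numerator and the patient leaves the denominator. Complications up to 30 days would likewise be compared in groups formed after randomization.

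The trial is meant to inform the choice between two anesthetics, and a non-inferiority result on delirium will be read beside the harm tables. If those tables rest on a set that events can alter, they cannot be relied on to show whether one drug causes more harm. Apart from this, two sections of the article give different analysis sets for the same outcomes.

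**Working it through.** **1. The two rules side by side.** The Eligibility criteria section covers all data and names modified ITT. The Statistical analysis section takes adverse events and non-delirium complications out of modified ITT and assigns intraoperative adverse events and non-delirium complications to per protocol. Both are current text and both cannot hold. Because the exception is stated twice, it reads as a choice rather than a slip.

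**2. What per protocol means here.** Modified ITT is described as ignoring adherence. A per-protocol set set against it would select on adherence. This is an inference from ordinary usage and from the contrast; no sentence in the article states it.

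**3. Can the event affect membership?** The Safety monitoring section foresees stopping the study drug because of an adverse event, so such a route exists.

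**4. Size within an arm.** The plan gives no figure on this point, so the inputs are assumptions. Let p be the true event risk, and s the share of event patients excluded from the per-protocol set because of the event. Assume that nobody without an event is excluded. Then

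reported risk = p(1 − s) / (1 − s·p)

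| True risk p | s = 0 | s = 10% | s = 25% | s = 50% |
|---|---|---|---|---|
| 10% | 10.0% | 0.090/0.990 = 9.1% | 0.075/0.975 = 7.7% | 0.050/0.950 = 5.3% |
| 5% | 5.0% | 0.045/0.995 = 4.5% | 0.0375/0.9875 = 3.8% | 0.025/0.975 = 2.6% |

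If patients without an event were excluded at the same rate s, the factor (1 − s) would cancel and the risk would be unbiased. The understatement arises when event patients are excluded preferentially.

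**5. Size between arms.** Take assumed true risks of 10% and 5%, a difference of 5.0 points:

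| s, higher-risk arm | s, other arm | Reported difference |
|---|---|---|
| 25% | 25% | 7.7 − 3.8 = 3.9 points |
| 50% | 50% | 5.3 − 2.6 = 2.7 points |
| 50% | 0 | 5.3 − 5.0 = 0.3 points |
| 25% | 50% | 7.7 − 2.6 = 5.1 points |

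The difference usually shrinks in these cases but need not. If both true risks were 10%, exclusion of 25% in one arm and 50% in the other would create a difference of 7.7 − 5.3 = 2.4 points where none exists.

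**6. Sample size.** The stated figures do not depend on the safety set. With z-values 1.960 and 0.842, a 10% margin and a 30% rate in both arms, n = (2.802)² × 2 × 0.30 × 0.70 / 0.10² ≈ 330 per group (337 at the quoted 31.1%). Then 330/0.95 = 347.4, rounded up to 348, or 696 in total. Changing the safety set alters none of this.

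**The case against.** The strongest reply is that the loss of patients is inferred. The article has no membership rule, and a full protocol or analysis plan that is not shown may define the set so that a patient stopped for harm stays in. Stopping is an action the protocol itself provides for, so it is not plainly a deviation. The Safety monitoring text is also narrow: it prints the word fetal, evidently for fatal, and does not speak of serious events in general. The article expects serious events to be rare and compliance to be high. All of this stands, and it makes the size of the bias unknown and possibly zero.

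It does not rescue the choice of set. Per protocol is what the article states for these outcomes, no all-treated safety set is described, and the conflict with the Eligibility criteria section remains under any definition.

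A reader might infer more than the documents support:

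- **That patients harmed by the drug are certain to be removed.** No sentence says so.
- **That undesired movement leads to a different hypnotic and so to exclusion.** The adverse-event grading mentions deeper anesthesia or analgesia, or more muscle relaxant. The anesthetic-care section discourages other hypnotics without prohibiting them. Neither a switch nor its status as a deviation is stated.
- **That the comparison must understate harm.** Preferential exclusion lowers the rate within an arm, but the difference between arms can move either way.
- **That the whole randomized comparison of harms is lost.** Hypotension burden, emergence agitation, delayed extubation, nausea and vomiting, and falls are separate secondary outcomes under modified ITT. Adverse events also go to the data monitoring committee, and serious ones to the ethics board, whatever the analysis set.

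**Conclusion.** The point holds in a limited form. The article contradicts itself on the analysis set for intraoperative adverse events and non-delirium complications, and the set named in the Statistical analysis section is a poor one for harms because the event can decide who is counted.

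Where event patients are preferentially excluded, within-arm rates are understated and the direction of the between-arm bias cannot be predicted. The size cannot be derived from the documents. The ranges above rest on assumed risks and exclusion shares, on per protocol having its ordinary meaning, and on no exclusion of patients without events. The primary delirium analysis is untouched.

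**What to change.** In the Statistical analysis section, replace the per-protocol approach for these outcomes with one named set: all randomized patients who received any study drug, compared by randomized arm. Add a supplementary table by drug actually received. If a per-protocol table is kept, label it supplementary. Word the opening sentence of that section to match.

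This set is not identical to the article's modified ITT, which excludes canceled surgery and withdrawn consent and does not condition on exposure. The Eligibility criteria section should therefore name the safety set as an explicit exception. For patients who withdraw after receiving study drug, the existing rule of using only the data they permit can apply.

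The cost is a short wording change in two sections, made before allocation is opened for analysis. It needs no new data, and enrolment stays at 348 per group.

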**Fig. 1 Fig1:**
[figure not shown]
The Consolidated Standards of Reporting Trials flow diagram

**Table 1 Tab1:** Overall schedule of participants

Timeline	Enrollment	Allocation	Post-allocation							
Timepoint	Within 72 h of admission	Surgery day	*Postoperative day*							
			*0*	*1*	*2*	*3*	*4*	*5*	*7*	*90*
Enrollment:										
Eligibility screen	X									
Informed consent	X									
Allocation		X								
Interventions:										
Propofol group		X								
Remimazolam group		X								
Assessments:										
Baseline variables	X									
Frailty, fall-down, and functionality assessment	X									X
Cognitive assessment (MoCA)	X								X*	X
Intraoperative data		X	X							
Intraoperative adverse events		﻿X	﻿X							
Delirium assessment (CAM-ICU, 3D-CAM)	X		X	X	X	X	X	X		
Quality of recovery				X						
Pain score and opioid requirement			X	X	X	X	X			
Postoperative neurologic and non-neurologic complications			X	X	X	X	X	X	X	X

^*^If the patient is discharged before POD 7, it is performed before discharge

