### Preoperative evaluation

Patient’s baseline demographic data will be collected and entered into a predetermined case report form (CRF), which includes the presence of delirium, sensory impairment (Morandi et al. 2021), alcoholism, history of depression, history of falls within 6 months, history of obstructive sleep apnea, level of education, functional status determined by the Barthel Activities of Daily Living index score (Mahoney and Barthel 1965), frailty score (Abellan van Kan et al. 2008), Charlson’s comorbidity index (Quan et al. 2011), type of surgery, neurologic deficit, polypharmacy (Hein et al. 2014), regular use of cholinergic antagonists, dopamine agent, lithium, benzodiazepine drug, floroquinolone, corticosteroid, or opioid analgesics. Preoperative laboratory results, including electrolytes and blood counts, will be recorded.

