#### Cognitive function test

Cognitive assessment will be conducted using Montreal Cognitive Assessment (MoCA) at baseline, 7 days after surgery or at discharge whichever comes first, and 3 months after surgery. Mini-mental state examination is the most widely used cognitive assessment tool for screening and diagnosing dementia; however, it lacks the sensitivity and specificity to detect subtle cognitive impairment (Needham et al. 2017). Therefore, we will use MoCA to detect minimal cognitive impairment (Nasreddine et al. 2005). It comprises six domains: Memory; Executive Functioning; Attention; Language; Visuospatial; and Orientation. Three months later, a telephone interview for the cognitive change will be performed using T-MoCA (Pendlebury et al. 2013), which omits visuospatial, executive, and memory functioning from the MoCA test. The occurrence of fall-down and associated injury and functionality using the Barthel ADL index within 3 months will be assessed using telephone interviews.

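### Three-month Barthel functionality falls under a rule that adjusts only for covariates found imbalanced, so the baseline Barthel score would almost never enter the comparison and some precision is given up.

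*Protocol article*

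**What the plan says.** **Outcome.** Item 12 of the Secondary outcomes reads "The occurrence of fall-down and associated injury and functionality at 3 months after surgery". The Cognitive function test section names the instrument and mode: "functionality using the Barthel ADL index within 3 months will be assessed using telephone interviews".

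**Baseline.** The Preoperative evaluation section lists "functional status determined by the Barthel Activities of Daily Living index score" among the data recorded before surgery, and Preoperative data collection repeats it. In Table 1 the row "Frailty, fall-down, and functionality assessment" is marked at enrollment and at day 90.

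**Analysis.** The Statistical analysis section contains three rules that bear on this outcome:

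- For continuous secondary outcomes: "Group comparison will be performed using a two-sample" t or Mann–Whitney U test, as appropriate.
- For adjustment, the authors will "adjust the effect of imbalanced covariates using a multivariable logistic regression model for count variables and linear regression or quantile regression for continuous variables". The threshold is given earlier in the section: "Acceptable covariate balance is defined as a standardized mean difference < 0.2 for the entire list of covariates".
- For longitudinal data: "Repeated measurements, such as NRS score for pain and sleep quality, daily cumulative opioid requirement, and cognitive function will be compared" by GEE. The outcomes named there are examples. Cognitive function is among them; functionality is not.

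**The concern.** The same scale is scheduled before surgery and at three months in every patient, yet the rule that most naturally covers the three-month score leaves the first measurement out unless the arms happen to differ on it. Patients who differ in function before surgery will tend to differ afterwards. An unadjusted comparison leaves that between-patient variation in the error term. The estimate is still valid, but its confidence interval is wider than the collected data require, and a real late difference in function is easier to miss.

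A covariate is worth adjusting for because it predicts the outcome, not because it is imbalanced by chance. Making adjustment depend on the observed SMD also makes the model depend on the data, which a fixed baseline covariate does not.

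**Working it through.** **Inputs**

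- Evaluable patients per arm: 330; enrolled per arm: 348 (Sample size).
- Two-sided significance level for secondary endpoints: 0.05 (Statistical analysis).
- Threshold for imbalance: SMD of 0.2 or more (the complement of the stated definition of acceptable balance).
- Correlation r between baseline and three-month Barthel: not in the documents, so assumed over a range.

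**The plan's own figure.** The protocol gives no precision or power figure for functionality. Its only size calculation is for the primary outcome. With a 10-point margin, one-sided alpha 2.5%, power 80% and unpooled variance, 30% in both arms gives 330 per arm. The quoted 31.1% gives 337, about 2% more. Then 330/0.95 rounds up to 348. So 330 is a fair basis for what follows.

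**Step 1: how often would the rule bring baseline Barthel in?** Under randomization the SMD of a baseline variable has standard deviation of about √(2/n).

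- n = 330: √(2/330) = 0.0778; 0.2/0.0778 = 2.57; two-sided tail probability 1.0%.
- n = 348: √(2/348) = 0.0758; 0.2/0.0758 = 2.64; two-sided tail probability 0.8%.

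**Step 2: what does always adjusting gain?** For linear adjustment on baseline, the variance of the group difference is multiplied by 1 − r². The unadjusted difference detectable with 80% power is (1.960 + 0.842) × √(2/330) = 0.218 SD. With adjustment this is multiplied by √(1 − r²). Power at 0.218 SD is Φ(2.802/√(1 − r²) − 1.960).

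| r (assumed) | Variance ratio | CI width ratio | Equivalent n per arm | Detectable difference (SD) | Power at 0.218 SD |
|---|---|---|---|---|---|
| unadjusted | 1.00 | 1.000 | 330 | 0.218 | 80.0% |
| 0.1 | 0.99 | 0.995 | 333 | 0.217 | 80.4% |
| 0.3 | 0.91 | 0.954 | 363 | 0.208 | 83.6% |
| 0.5 | 0.75 | 0.866 | 440 | 0.189 | 89.9% |
| 0.7 | 0.51 | 0.714 | 647 | 0.156 | 97.5% |

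**Step 3: how much of that does the planned rule recover?** A simulation (6,000 trials for each r, 330 per arm, normal scores) compared the standard error with that of the unadjusted test.

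| r (assumed) | Adjust only if SMD ≥ 0.2 | Always adjust |
|---|---|---|
| 0.3 | 0.996 | 0.955 |
| 0.5 | 0.988 | 0.870 |
| 0.7 | 0.976 | 0.712 |

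At r = 0.5 the rule reduces the standard error by 1.2% where 13.0% is available, so more than nine tenths of the gain is lost. The other two rows show about the same fraction.

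**The case against.** **The GEE list is open.** Functionality is measured twice in Table 1, so it could be read as a repeated measurement and sent to GEE. This stands as an ambiguity. The sentence nevertheless names cognitive function and not functionality, and the Secondary outcomes describe cognition in terms of change but functionality as a state at three months. At best the text supports two analyses of one outcome.

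**This is detail for the analysis plan.** The article is a condensation, and Data management refers to a predefined statistical plan that is not shown. That plan may already settle the matter. But the article does not stay silent: it states the test, the condition for adjustment and the threshold. The point is about that stated rule.

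**An unadjusted test in a randomized trial is valid.** This stands in full. The issue is efficiency, not error.

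**The size rests on an unknown r.** This also stands. These are elective patients, and if most score at or near the Barthel maximum, r could be low and the gain close to nil. The 1 − r² figures apply to linear adjustment compared with a t test. They do not carry over to a proportional-odds model, where adjustment also changes the quantity estimated, nor directly to the Mann–Whitney option.

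**Two stronger readings do not hold.** A reader might infer that the plan offers only a raw test; in fact it offers linear or quantile regression, though on a trigger that would rarely fire for this covariate. A reader might also infer that the in-hospital MoCA has the same weakness. It does not: cognitive function is explicitly assigned to GEE, and nowhere is a raw change-score test planned.

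**Conclusion.** The point holds as a minor improvement. On its most natural reading, the stated rule would use baseline Barthel in about 1% of trials, although the score is to be collected in every patient. Under linear adjustment the variance given up is r²: about 1%, 9%, 25% and 49% for r of 0.1, 0.3, 0.5 and 0.7.

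This rests on four assumptions: that the Barthel score is handled as continuous, that imbalance means an SMD of 0.2 or more, that functionality is not read into the GEE list, and that r lies somewhere in the range shown.

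It would be wrong to infer that the three-month comparison is biased or that the trial's main conclusion is at risk. The consequence is confined to the precision of one secondary outcome; the primary analysis and the sample size are untouched.

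**What to change.** Add one sentence to Statistical analysis: three-month Barthel will be analysed by regression on treatment arm with baseline Barthel as a prespecified covariate, whatever the observed balance. Name the model in advance, for example linear regression with robust standard errors, or an ordinal or quantile model if scores are expected to be strongly skewed. Keep the unadjusted test as a supporting display. The same sentence should make clear that functionality is not part of the GEE set, so that only one main analysis remains.

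The cost is one sentence and no new data or patients; linear and quantile regression are already in the plan. The price is a model-based estimate in place of a simple test, for a gain that may be small if scores cluster at the ceiling.

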## Abstract

**Background:**

Remimazolam is a short-acting benzodiazepine newly approved for the induction and maintenance of general anesthesia. Remimazolam emerges as an ideal drug for the neurosurgical population due to its rapid emergence, enabling early neurological assessment, and its ability to maintain perfusion pressure, which is crucial for preventing cerebral ischemia. However, the use of benzodiazepine has been associated with an increased risk of postoperative delirium (POD). There is currently limited evidence about the relationship between remimazolam-based total intravenous anesthesia (TIVA) and POD.

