### Intervention

Patients in the remimazolam group will be administered a loading dose of 0.1 − 0.2 mg/kg intravenously, followed by a continuous infusion of 1 − 2 mg/kg/h until the end of surgery. Flumazenil (100 − 500 mcg) will be administered to wake the patients at the end of surgery until they show eye-opening and simple obeying. Patients in the propofol group will receive general anesthesia using a target-controlled infusion (TCI) of propofol with an effect site concentration of 3 − 5 μg/mL until the end of surgery. In both groups, remifentanil will be co-administered using a TCI mode. Anesthetics in each group will be adjusted by attending anesthesiologists with reference to the bispectral index (BIS), heart rate, and blood pressure.

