#### Intraoperative data collection

Intraoperative measures, including operative and anesthesia time, anesthetic concentration, perioperative use and dosage of sedatives and opioids, electroencephalographic (EEG) data, hemodynamic data, use of inotropic or vasopressor agents, use of a chronotropic agent for the treatment of bradycardia, total infused volume of crystalloid, transfusion, estimated blood loss, and urine output, will be obtained from patients’ electronic medical records.

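### Duration of anesthesia is a post-randomisation variable that the drug may change, so it is unsuitable as a subgroup for judging consistency of the primary outcome

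*Protocol article*

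**What the plan says.** The Statistical analysis section gives the purpose: "Subgroup analyses will be conducted to assess the consistency of differences in the primary outcome". It presents the factors as defining different patient populations. The list runs through age, sex, surgery type, preoperative cognitive impairment and ASA status, and closes with "duration of anesthesia, alcohol abuse, or preoperative benzodiazepine use within 24 h".

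The Intraoperative data collection section places this variable among data that arise during the operation: "Intraoperative measures, including operative and anesthesia time, anesthetic concentration".

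Three places link the drug to the end of the anesthetic:
- The Abstract says "Remimazolam emerges as an ideal drug for the neurosurgical population due to its rapid emergence".
- The Background section makes the same point about quick arousal, even after long use.
- The Intervention section describes flumazenil, which "will be administered to wake the patients at the end of surgery until they show eye-opening and simple obeying", for the remimazolam group only.

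**The concern.** A subgroup analysis compares the randomised arms fairly only if membership is fixed before treatment or cannot be altered by it. The other seven listed factors describe the patient or the planned operation before anesthesia starts. Duration of anesthesia does not.

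Suppose remimazolam shortens the anesthetic. A remimazolam patient then needs a longer operation than a propofol patient to fall in the long stratum, and some patients who would have been long under propofol fall in the short stratum. Within each stratum the remimazolam patients have had the longer surgery. If longer surgery goes with more delirium, remimazolam looks worse in both strata. If the drug lengthens the anesthetic, the sign reverses and remimazolam looks better in both, which is the flattering direction in a non-inferiority trial.

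What is at stake is the reading of this one supporting analysis. A reader could not tell an artefact of the split from a real effect within long or short cases.

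**Working it through.** **Inputs from the article.** Sample size section: incidence 31.1%, margin 10 points, 330 analysed per group. The 330 is the result at an incidence of 30%; the same formula gives 337 at 31.1%, within 3%, and nothing here turns on that. The article gives no figure for the effect of the drug on duration, for the spread of duration, or for its relation to delirium.

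**Assumptions.** Let X be surgical time in SD units, standard normal in both arms. Delirium risk is r(x) = 1/(1 + exp(−(a + bx))), the same in both arms, so the true drug effect is zero. The constant a is set so that mean risk is 31.1%. Anesthesia duration is X under propofol and X − d under remimazolam. The split is at the pooled median, which is −d/2.

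**Formula.** Remimazolam patients are long if X ≥ d/2; propofol patients are long if X ≥ −d/2. The false differences (remimazolam minus propofol) are

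- long: E[r(X) | X ≥ d/2] − E[r(X) | X ≥ −d/2]
- short: E[r(X) | X < d/2] − E[r(X) | X < −d/2]

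**One case in full: b = 0.7 (odds ratio about 2 per SD), d = 0.3.** Here a = −0.88. Numerical integration gives:

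- long: 43.82% − 40.73% = +3.1 points
- short: 21.09% − 18.86% = +2.2 points
- share long: 44.04% with remimazolam, 55.96% with propofol
- overall, remimazolam: 0.4404 × 43.82 + 0.5596 × 21.09 = 31.1%
- overall, propofol: 0.5596 × 40.73 + 0.4404 × 18.86 = 31.1%

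The overall difference is 0, yet both strata show remimazolam as worse.

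**Range (long / short stratum, points).** Minutes assume an SD of 80 min.

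| Shortening d | b = 0.3 | b = 0.7 | b = 1.0 |
|---|---|---|---|
| 0.1 SD (8 min) | 0.4 / 0.4 | 1.0 / 0.7 | 1.5 / 0.9 |
| 0.3 SD (24 min) | 1.3 / 1.1 | 3.1 / 2.2 | 4.4 / 2.8 |
| 0.5 SD (40 min) | 2.2 / 1.9 | 5.1 / 3.7 | 7.3 / 4.6 |

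**What the artefact does to inference.** Take about 330/2 = 165 patients per arm per stratum, b = 0.7 and d = 0.3. The gap between strata is only 3.1 − 2.2 = 0.9 point. Its standard error is √[(0.438×0.562 + 0.407×0.593 + 0.211×0.789 + 0.189×0.811)/165] = 7.0 points. A two-sided 5% interaction test then rejects about 5.2% of the time (5.5% at d = 0.5), which is negligible inflation. The damage is to the within-stratum comparisons: a two-sided 5% test within a stratum rejects about 8 to 9% of the time at d = 0.3 and 13 to 15% at d = 0.5.

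**The case against.** The strongest reply is that the effect is probably small. Both infusions continue through to the end of the operation, so surgery sets most of the duration and the drug acts mainly on induction and wake-up. If the SD is 80 min, 0.3 to 0.5 SD means 24 to 40 min saved, which the article does not suggest. At 5 to 10 min the false differences are about 0.2 to 1.8 points for slopes of 0.3 to 1.0. The model also makes duration an exact measure of surgical time; other sources of variation would dilute the artefact. All of this stands and limits the size. It does not make duration a baseline factor.

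It can also be said that the split creates almost no false heterogeneity, since both strata move the same way. That is right for an interaction test. It does not help a reader who takes the stratum estimates at face value and sees both differ from the overall result.

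Some stronger readings are tempting but not supported:

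- **That delayed extubation, a secondary outcome, shows the drug will change anesthesia time.** The Anesthetic care section lets patients go to the ICU still intubated, and the article does not define where anesthesia time ends. Late extubation need not lengthen it.
- **That the alcohol-abuse subgroup is largely emptied by the exclusion "6) dependency on psychiatric drugs or alcohol".** That criterion concerns dependency, while the subgroup concerns abuse. Abuse short of dependency remains eligible, alcoholism is still recorded at baseline, and no prevalence is given. At most the subgroup overlaps an exclusion criterion and may be small.
- **That missing cut-points or interaction tests are a fault.** A condensed article commonly leaves these to the full protocol or analysis plan.

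**Conclusion.** The point holds for duration of anesthesia. It is a post-randomisation variable which, on the article's own account of emergence, the assigned drug may change. A split on it cannot serve as evidence that the primary result is consistent.

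The size is uncertain and may be modest: about 0.4 to 1 point for a shift of 0.1 SD with a slope of 0.3 to 0.7, and about 3 to 5 points in the long stratum for 0.3 to 0.5 SD with a slope of 0.7. These figures assume a normal surgical time that is prognostic for delirium, a constant shift and a median split; none of these comes from the article. The sign depends on whether the drug shortens or lengthens the anesthetic.

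A reader might infer that the trial's main conclusion is at risk. It is not: non-inferiority rests only on the overall upper 95% limit being below 10%, no decision rule is attached to the subgroups, and the overall difference in the calculation is 0.

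**What to change.** Remove duration of anesthesia from the subgroup list for the primary outcome. To examine long versus short procedures, use a factor fixed before randomisation: surgery type, which is already listed, or scheduled operation time. If the split on actual duration is kept, label it exploratory, state that it is defined after randomisation, and do not present it as evidence of consistency.

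The change is to wording, best made before the allocation is opened so that it cannot look driven by results. Surgery type needs no new data. Scheduled operation time is not among the preoperative data that the article lists, so it would have to be taken from the operating schedule if it is not already held. The price is that actual duration is no longer examined as a confirmatory-style subgroup. The primary analysis and sample size do not change.
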